**FIGURE 2 F2:**
[figure not shown]
Trexo Plus pediatric lower-limb exoskeleton, mounted on a medium-sized Rifton Pacer Gait trainer. Lateral **(left)** and anterior **(right)** views are shown. Exoskeleton battery, motors at the hip and knee, and shin cuffs are indicated. Rifton frame, steering guide bar, and chest prompt are also indicated. Trexo orientation is set-up for child to be facing out of the open side of Rifton frame. Tablet interface for controlling the robotic legs is not shown.

#### 2.4.2 Physiotherapy team training and treatment strategy

The Trexo device will be a new physiotherapy intervention tool for physiotherapists. As such, to ensure safe, effective, and competent use that aligns with the child’s abilities and individualized gait goals, PT/PTA training will include: (i) vendor-created technical materials and virtual training from the Trexo company; (ii) in-person shadowing of Trexo use at a community clinic; (iii) motor-learning strategies online educational materials created at our center and based on the Motor Learning Strategies Rating Instrument (Ryan et al., 2019, 2020; Spivak et al., 2021); (iv) Trexo piloting with typically developing children; and (v) ongoing peer-mentoring process within our center.

Trexo physiotherapy sessions will use an incremental progression process consistent with a motor learning approach, with increasingly challenging tasks presented over time (Figure 3). Participants may also perform exercises (i.e., stretching) to a maximum of 10 additional minutes at the start of the session that may be helpful in these sessions to facilitate the child’s comfort in the Trexo. Principles of motor learning (intensity, repetition, variability, task-specificity, etc.), and the parent’s and PT’s structured goals (described in section “2.6.2 Functional priority goals”) will be prioritized during sessions. In each session, the PT/PTA team will work together with the child and Trexo. The PT/PTA will self-select between the roles of (i) steering the exoskeleton and (ii) operating the Trexo tablet and motivating the child. A safety monitoring plan will be in place throughout each Trexo session to mitigate and/or respond to any adverse events (section “2.10 Adverse events”).

**FIGURE 3 F3:**
[figure not shown]
Sample of physiotherapy progression throughout duration of 12 Trexo intervention sessions. Choice of incremental challenges (through Rifton or exoskeleton adjustments) can be tailored to the participant and their individual response to therapy.

#### 2.4.3 Outpatient physiotherapy program

Participants in the outpatient cohort will receive two individual Trexo-based physiotherapy sessions per week (30-min sessions active treatment time excluding initial Trexo set-up time). The session will be led by one of the study’s Trexo-trained PTs along with a Trexo-trained assisting PTA. These clinicians will not necessarily be previously familiar with the child, being assigned instead according to family and PT/PTA availability. To ensure safe and effective communication with the child, parents will be present at all sessions and will help interpret communication and fatigue as needed while the child is in the Trexo. For each session, 60 min will be allocated to setup, Trexo-based physiotherapy, and session feedback documentation by the PT/PTA. Sessions will occur in the center’s gait lab, hallways, or outdoors in the summer months.

#### 2.4.4 In-school physiotherapy program

Participants in the school cohort will receive two Trexo-based sessions per week (20-min sessions active treatment time excluding initial Trexo set-up time) from their school-affiliated physiotherapy team, to be integrated within a typical school week. The PT/PTA feedback documentation will be done at the end of the school day. One Trexo session will be done in gym class (participation opportunities for peer-based activities), and one done individually in the school’s activity center. Parents are not typically present at regular physiotherapy sessions in this school setting. Thus, the child’s usual school PT will provide the Trexo intervention to ensure that the child has a familiar service provider. This PT will have undergone the Trexo user training. The Trexo-trained PTA for these sessions will be assigned based on availability and will not necessarily be previously known to the child.

### 2.5 Feasibility and acceptability indicators

Feasibility and safety will be quantitatively measured by a set of key process, management, and resource indicators (Tickle-Degnen, 2013; Ameis et al., 2020; Ayoub et al., 2020; Hilderley et al., 2022) with associated targets set for this study protocol. A priori targets for feasibility and acceptability are: (i) ability to enroll 80% of eligible participants that are invited to participate in the study; (ii) study retention rate of ≥ 90%; (iii) completion of awake MRIs ≥ 50%; (iv) tolerance (of setup and wear) and retention of muscle recording sensors during walking tests ≥ 75%; (v) tolerance and retention of heart rate sensor chest strap wear during gait (Trexo walker and regular walker) and motor/functional assessment ≥ 75%; (vi) tolerance of motor/functional assessments ≥ 90%; (vii) completion of parent and PT/PTA interviews ≥ 75%; (viii) adverse events “mild” severity at most and occur in ≤ 10% of physiotherapy sessions; (ix) Trexo set-up time and pauses due to adjustments significantly decrease over 12 physiotherapy session duration; (x) Trexo software or device glitches occur in ≤ 5% of sessions; (xi) motor learning strategies used “often” (25–49% of time) by PT/PTA team during physiotherapy sessions; (xii) child comfort and task enjoyment self-ratings during physiotherapy sessions reflect ≥ 80% positive scoring; (xiii) perceived study benefit by parent/clinician ≥ 80% positive scoring; and (xiv) PT/PTA training and session satisfaction ratings ≥ 80%.

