**FIGURE 1 F1:**
[figure not shown]
Flow chart of study visits and timeline, reflecting O_0_ X O_1_ O_2_ design.

**TABLE 1 T1:** Research team member designations and corresponding roles in the study.

Designation	Role
Principal investigators	Responsible for study oversight and adverse event management.
Study researchers	Non-PT team members that are responsible for coordinating recruitment, scheduling, non-PT data collection, and data analysis.
Study physician	Center-affiliated pediatrician that helps with diagnostic expertise, recruitment, eligibility, and adverse event management.
Treating PTs/PTAs	Physiotherapy team members that are Trexo-trained and complete the 12 Trexo (twice weekly) intervention sessions.
PT assessors	Independent PTs (different from treating PTs) that complete the physical screening and motor/functional assessments.
Study interviewer	Independent team member that hosts all Zoom-based interviews.
MRI technician	Centre-affiliated technician that operates MRI scanner.

During ‘**O’ phases (pre/post intervention)**, participants will do their usual physiotherapy regimen (with their usual assistive device, where applicable) and associated home program, and will undergo the set of study assessments (gross motor/functional assessments and neuroimaging) in this approximately 2–3-week period pre- and post-Trexo use (Phase X). One-month post O_1_, participants will have one final motor/functional assessment and neuroimaging visit (O_2_). They will continue with their usual physiotherapy regimen during the month between O_1_ and O_2_.

**Intervention ‘X’ phase** will consist of the Trexo physiotherapy block: physiotherapy sessions twice weekly (30-min sessions excluding initial set-up time) for 6 weeks provided by a study-trained PT/Physiotherapist Assistant (PTA) team within a goal-based training program that is grounded in motor learning principles. Trexo physiotherapy will be integrated within a school-based program for half of the study cohort (*n* = 5), and within an outpatient program for the other half (*n* = 5). Each child will receive 1–2 acclimatization/fitting sessions in the Trexo before starting physiotherapy sessions. Walking tests and muscle recordings at the start and end of this phase will be done in the Trexo and in the child’s usual non-robotic wheeled walker (if they use one) for comparison and for assessment of potential carryover effects from Trexo use to their wheeled walker.

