#### 2.2.4 Sample size justification

The planned sample size of 10 children for this feasibility study will be sufficient to give an initial group picture through descriptive statistics and summary graphs of feasibility indicators and quantitative outcomes. This aligns with other quantitative pediatric therapy technology-based intervention studies that have successfully provided meaningful feasibility study results with 4 to 20 participants: (Richards et al., 1997; Wallen et al., 2008; Weightman et al., 2011; Radtka et al., 2013). This sample size will also elucidate how a single robotic assistive device may be shared (i.e., fitting adaptations to support use) among multiple children for use as a physiotherapy intervention within a center.

For the qualitative user perspective data, there is no agreed-upon sample size to achieve saturation in qualitative research (Saunders et al., 2018), instead depending collectively on sample homogeneity, interaction quality, and theoretical framework (Malterud et al., 2016).

Previous qualitative descriptive studies with children, parents, or clinicians reporting on user experiences of applying new technology or outcome measures have produced meaningful results with samples of 5 to 13 participants (Rich et al., 2014; Beveridge et al., 2015; Phelan et al., 2015; Kahlon et al., 2019; Vaughan-Graham et al., 2020; Giancolo et al., 2022; Hadj-Moussa et al., 2022; Torchia et al., 2023).

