### 2.3 Participant enrolment

#### 2.3.1 Invitation letters from circle of care

Pediatricians, PTs, and clinic staff affiliated with the hospital-based outpatient program and the school integrated education therapy program will share study invitation letters with parents of the children on their caseload who meet the main eligibility criteria. Interested parents will have an initial phone conversation with the study’s research coordinator who will provide them with full details on the study, and if they are interested in moving ahead, will then review the study’s basic eligibility questions. If these criteria are met, they will be added to a candidate list that will be capped by a predetermined date deadline. If the list exceeds capacity, names will be drawn by a random number system (randomizer.org) to schedule an in-person physical screening visit to confirm eligibility.

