#### 2.5.1 Recruitment, retention and adherence

Recruitment rate will be calculated as the percentage of participants enrolled as a function of the number of participants invited. Study retention will be calculated as the enrolled participants who complete all required parts of the study as a function of total enrolled participants. Tolerance will be defined as procedural adherence for each methodology, whereby completion of each of the various measurement and intervention components will be carefully considered for planning of future interventions. The acceptability of physiotherapy intervention frequency of twice per week will be assessed based on attendance and family feedback.

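### The 80% recruitment target and the formula for the recruitment rate use different denominators, and under the formula 80% is out of reach once 13 or more families are invited

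*Protocol article*

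**What the plan says.** Section 2.5 lists 14 a priori targets. The first is the "ability to enroll 80% of eligible participants that are invited to participate in the study". Section 2.5.1 gives the calculation: "Recruitment rate will be calculated as the percentage of participants enrolled as a function of the number of participants invited".

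The order of events is in sections 2.3.1 and 2.3.2. Clinic and school staff "will share study invitation letters with parents of the children on their caseload who meet the main eligibility criteria". Interested parents then answer basic eligibility questions by phone. If the answers are suitable, the family joins a list of candidates, which closes on a date fixed in advance. For a surplus of candidates over places, the rule is: "If the list exceeds capacity, names will be drawn by a random number system (randomizer.org) to schedule an in-person physical screening visit". Parents give written consent before the physical screening, and the study physician confirms eligibility after it.

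Section 2.2.4 fixes the number of places: "The planned sample size of 10 children for this feasibility study". Section 2.10 rules out replacing children who drop out. Section 2.11.1 says that the indicators will be compared with their targets.

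**The concern.** The target and its formula describe different quantities. Children who pass a first look by clinic staff can still be excluded by phone, on physical measurement or at MRI screening. They leave the denominator of the target but stay in the denominator of the formula. If the choice between the two is made once the counts are known, the target is no longer a priori.

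The second difficulty is the limit on places. The number of letters has no stated limit and the candidate list closes by date, not by number. The protocol foresees more candidates than places and removes the surplus by lot. A family that was invited, wanted to take part and was not drawn counts under the formula in the same way as a family that refused. Strong demand could then be reported as weak recruitment, in a study meant to inform later multi-center research.

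**Working it through.** The 80% is a chosen threshold with no derivation, so there is no planned figure to reproduce. The check is arithmetic on the two definitions.

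**Inputs from the article:** target 80% (2.5); formula enrolled / invited (2.5.1); at most 10 enrolled (2.2.4, with no replacement under 2.10). Section 2.3.1 does not put a number on capacity, so I take it as the planned 10.

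**Assumed inputs:** the article gives no number of families invited, eligible or willing. The counts below are illustrations.

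**Step 1: do the two denominators give the same verdict?** Take 15 invited, 10 eligible, all 10 willing and enrolled. No draw is needed.
- Target wording (2.5): 10/10 = 100%, met.
- Formula (2.5.1): 10/15 = 66.7%, missed.

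**Step 2: what is the highest rate the formula allows?** With M families invited and 10 places, the ceiling is min(10, M)/M. For 80% we need M ≤ 10/0.80 = 12.5, so M can be at most 12.

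| Invited (M) | Highest possible rate | 80% attainable? |
|---|---|---|
| 10 | 100% | yes |
| 11 | 90.9% | yes |
| 12 | 83.3% | yes |
| 13 | 76.9% | no |
| 15 | 66.7% | no |
| 20 | 50.0% | no |
| 30 | 33.3% | no |

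**Step 3: does restricting to eligible children cure this?** Take 20 invited, 16 eligible, all 16 willing, 10 enrolled and 6 not drawn.
- Formula (2.5.1): 10/20 = 50%.
- Target wording (2.5), undrawn families counted as eligible: 10/16 = 62.5%.
- Target wording (2.5), undrawn families left out because they were never confirmed eligible: 10/(16 − 6) = 100%.

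The same fully willing group passes or fails on a point that neither section settles.

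**The case against.** **Letters are already filtered.** They go only to families who meet the main criteria, so the invited in 2.5.1 might be shorthand for the eligible invited in 2.5. This narrows the gap but does not close it: children excluded by phone or at screening still separate the two.

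**The limit on places need not affect the target as worded in 2.5.** The draw comes before eligibility is confirmed, so undrawn children are never confirmed eligible and may drop out of that denominator. This stands. A reader might infer that the target must fail under both definitions whenever interest is high. The text does not support that. The ceiling follows from the 2.5.1 formula; under 2.5 there is only an ambiguity. Even under the formula, 11 or 12 invited families do not force a miss.

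**Invited might mean invited to screening after the draw.** No section says so, and 2.3.1 uses the word for the letter that comes before it.

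**More candidates than places may never occur.** Entry is narrow and recruitment comes from one outpatient and one school program. That is fair, and the counts above are assumptions. But a low-interest round with many letters meets the same ceiling, and the mismatch in Step 1 needs no draw at all.

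**The split by setting.** Section 2.1 places children "within a school-based program for half of the study cohort (*n* = 5), and within an outpatient program for the other half (*n* = 5"), and a reader might infer that a single lottery would upset this balance. The article does not describe one draw across both settings. Drawing within each setting fits its wording, and the draw selects for screening, not enrolment. I do not raise this as a fault.

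**Conclusion.** The point holds in this form. The target in 2.5 and the formula in 2.5.1 use different denominators and can give opposite verdicts on the same data (100% against 67% in the illustration). Under the formula as written, 80% cannot be reached once 13 or more families are invited, however willing they are. Under the target's wording, the treatment of undrawn families is undefined.

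The size rests on reading capacity as 10 and invitation as the letter. How far the rate would fall depends on the number invited, which the article does not give.

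This should be fixed but is not critical. It concerns one of 14 indicators, summarised descriptively, with no stopping or progression rule attached. It does not touch the co-primary outcomes or safety.

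**What to change.** Use one definition in 2.5 and 2.5.1. It should exclude children found ineligible, not count willing families who were not drawn as recruitment failures, and keep families who decline at the letter, phone or consent stage in the denominator. One version that does this:

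- **Target (80%):** (enrolled + willing but not drawn) / (invited families not found ineligible).
- **Separate line, without the target:** enrolled / (drawn and not found ineligible).
- **Counts to report:** invited, interested, not drawn, screened, ineligible, declined, enrolled.

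On assumed counts, the target measure behaves as intended:
- 15 invited, 5 found ineligible, 10 enrolled: 10/10 = 100%.
- 20 invited, 4 found ineligible by phone, 10 enrolled, 6 willing but not drawn: (10 + 6)/16 = 100%.
- 20 invited, 4 found ineligible, 8 willing and all enrolled: 8/16 = 50%, a miss that reflects families declining.

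Dividing enrolled children by those drawn, screened and confirmed eligible would not serve. Written consent comes before screening, so that ratio would be near 100% by construction and would hide families who decline.

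The cost is the wording of one target and one definition, and a log of counts at each recruitment stage. No extra data are needed from participants.

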### 2.11 Data analysis

#### 2.11.1 Quantitative data analysis

*Feasibility/safety/acceptability indicators* (section “2.5 Feasibility and acceptability indicators”) will be summarized for each child’s sessions and the group descriptive statistics will be compared to *a priori* target values.

*Motor/functional assessment measures and functional priority goals* will have total/dimension scores summarized via descriptive statistics. Paired *t*-tests or non-parametric equivalents will be conducted for baseline and post-intervention time points for the co-primary measures (GMFM-88 and COPM goals), and then with each of the secondary outcomes. Correlational analyses (Pearson’s r) will also be undertaken to investigate associations between primary and secondary outcomes or with MRI results. Each clinical measure will be graphically inspected for any patterns from baseline to the optional 1-month post-intervention timepoint. For a subsample of children (undetermined subgroup ‘n’ at this point), comparisons will also be made between walking performance in the child’s regular walker and the Trexo at baseline and post-intervention.

*MRI scans* will be processed with Freesurfer Software (surfer.nmr.mgh.harvard.edu), employing a longitudinal pipeline. Automated segmentation of structural T1-weighted images will be performed, followed by quality control steps to ensure image clarity. Any neuroimaging data with excessive motion artifact will be excluded from the study. Regions of interest (ROI) will be selected based on brain areas that are most associated with gait, motor function, and motor learning. From T1 anatomical data, mean cortical thickness per brain region, and white and gray matter volumes will be calculated. Diffusion data will be used to identify and reconstruct relevant white matter tracts as well as derive DKI and DTI mean metric maps, kurtosis fractional anisotropy (FA) values, and mean kurtosis (MK), as outcome measures. From the fMRI data, ROI-specific time courses of the BOLD signal will be computed by averaging time courses across voxels within each ROI. fMRI outcome measures will include functional connectivity (FC) correlation matrices and a structural-decoupling index.

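### Read literally, feasibility targets (ix) and (xi) can score good delivery as a miss, and (viii) can be met while mild adverse events concentrate in one child

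*Protocol article*

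**What the plan says.** Section 2.5 lists fourteen a priori targets. Three matter here:

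- (viii) Adverse events are to be mild "severity at most and occur in" no more than 10% of physiotherapy sessions. The unit is the session, and no per-child limit is given.
- (ix) "Trexo set-up time and pauses due to adjustments significantly decrease over 12 physiotherapy session duration". No absolute time is given.
- (xi) Motor learning strategies are to be used 'often', printed as "25–49% of time) by PT/PTA team during physiotherapy sessions". The target has a lower and an upper edge. Most of the other numeric targets carry a ≥ or ≤ sign.

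Section 2.11.1 says how the targets are applied. Indicators are summarised for each child's sessions, "and the group descriptive statistics will be compared to" the a priori values.

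Other sections bear on how the targets behave:

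- Section 2.1 gives each child one or two fitting sessions before session 1.
- Section 2.4.2 has staff pilot the device beforehand and gives priority to motor learning principles in sessions.
- Section 2.8.4 has a stored adjustment profile applied before each session.
- The Figure 3 legend describes progression: "Choice of incremental challenges (through Rifton or exoskeleton adjustments) can be tailored to the participant and their individual response to therapy".

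**The concern.** A feasibility target should be met when delivery is good and missed when it is poor. As printed, these three do not always do so.

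- **(xi)** More of the intended ingredient, once past 49% of time, becomes a miss.
- **(ix)** Improvement is rewarded, not adequacy. A team that starts slowly can pass, and a team that is quick from the outset almost cannot. Planned progression through device adjustments may also add pauses that count against the target.
- **(viii)** Pooling over sessions lets recurrent mild events in one child be diluted by nine children without events.

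Feasibility, safety and acceptability are the first study objective. Section 3 makes later extension to non-ambulatory children conditional on adequate safety and acceptability. A reader of the results will look first at which targets were met.

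**Working it through.** **Number of sessions.** Section 2.2.4 gives the sample: "The planned sample size of 10 children for this feasibility study". Section 2.1 gives "physiotherapy sessions twice weekly (30-min sessions excluding initial set-up time) for 6 weeks", so 2 × 6 = 12 sessions per child, which reproduces the 12 stated in the Figure 3 legend. The full total is 10 × 12 = 120. (Section 2.4.4 gives 20 minutes for school sessions; this does not change the count.)

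**Target (viii).** Suppose one child has a mild event in every session received and the other nine have none.

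- All 12 sessions: 12/120 = 10.0%, met exactly at the limit. The mean of the ten child percentages is (100 + 9 × 0)/10 = 10.0%, the same result.
- One session missed by another child: 12/119 = 10.08%, not met. One other child absent throughout: 12/108 = 11.1%, not met.
- Events in 11 of 12 sessions: 11/120 = 9.2%, met. It is still met with ten sessions missed elsewhere (11/110 = 10.0%).
- The affected child stopped early, denominator 108 + k: k = 4 gives 4/112 = 3.6%, k = 6 gives 6/114 = 5.3%, k = 8 gives 8/116 = 6.9%. All are met.

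The full-block case is a knife edge. The early-stop cases are not, because stopping removes that child's remaining sessions from the denominator.

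**Target (ix).** The article gives no test, alpha, set-up time or SD. A two-sided 5% test is assumed.

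- No true change in set-up time: the chance of a significant decrease is 0.05/2 = 2.5%, so about 97% of such studies miss the target. A simulated slope test on a flat set-up time gave 2.7%. If pauses must fall as well, the chance cannot be higher.
- True decrease, paired first-versus-last comparison, n = 10, noncentral t: power is 29% for a mean fall of 0.5 SD of the differences, 62% at 0.8 SD and 80% at about 1.0 SD.
- Long set-up that shortens, assumed to fall from 30 to 20 minutes with SD 5 between and within children: significant in essentially 100% of simulations, although set-up at the end is still long.

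**Target (xi).** Values checked against the printed band and against a floor of 25%:

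| Time using strategies | 25–49% as printed | 25% or more |
|---|---|---|
| 20% | missed | missed |
| 25%, 37%, 49% | met | met |
| 50%, 60%, 75% | missed | met |

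**The case against.** **Stakes.** A reader might infer that these targets decide whether delivery is judged feasible and safe. The article does not say so. There are fourteen indicators, results are compared with targets, and quantitative and qualitative findings are then presented together. That objection stands.

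**(viii).** A reader might infer that repeated harm to one child counts as success. The target also requires every event to be mild. Section 2.5.2 records skin irritation before and after each session and tracks the severity and duration of pain. Section 2.10 involves the study physician and provides for discontinuation. Section 2.11.1 already summarises indicators by child. An affected child would therefore be seen. What remains is narrower: the line for the target could still read as met.

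**(ix).** The device is new to the physiotherapists, so tracking a learning trend is reasonable. The missing test may be specified in an analysis plan that is not shown, and its absence is not counted here. It is tempting to say that adjustment pauses should rise with progression, but that is not established: settings can be changed by tablet, and physical adjustments are made before the session starts. The documents support only that planned adjustments may add pauses.

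It is also tempting to read a set-up limit from the outpatient slot, where "60 min will be allocated to setup, Trexo-based physiotherapy, and session feedback documentation by the PT/PTA". Subtracting 30 minutes of treatment leaves 30, or 20 if the optional stretching (up to 10 minutes) falls inside the slot, which is not stated. The remainder must also cover documentation, and the slot is for outpatients only. No single limit follows.

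**(xi).** The band is probably a rating category, and the authors may well mean at least 'often'. Target (i) also lacks a ≥ sign and is plainly a floor. But (xi) prints an upper edge and (i) does not.

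**Conclusion.** The point holds on the printed wording, with limits.

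- **(xi)** misses every value of 50% or more if the band is applied literally. No assumption beyond literal reading is needed.
- **(ix)** would be met only about 2.5% of the time by set-up that is short and stable from session 1, and would usually be met by long set-up that falls clearly. The 2.5% rests on an assumed two-sided 5% test and no true change; the 30-to-20-minute example rests on assumed times and SDs. The target does not fail all good delivery.
- **(viii)** can be met with all events in one child. At 12/120 this needs all sessions held, mild events only and none in other children. It is easier if that child stops early (6/114 = 5.3%).

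The accurate statement is that these targets can mislead, not that they always do. Because no go/no-go rule hangs on any one of them and child-level data are already planned, this is a worthwhile, inexpensive improvement and not a must-fix.

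**What to change.** - **(xi)** Reword to: at least 'often' (25% of time or more).
- **(ix)** Replace the significance requirement with an absolute limit on late-session set-up time, naming in advance which sessions count as late. The investigators should set it separately for the outpatient and school settings. Report the change over the 12 sessions as an estimate with a 95% CI; the mean of the per-child slopes is enough with ten children. Count pauses for fit or fault separately from pauses for planned progression.
- **(viii)** Keep the session rate. Beside it, report the number of children with any adverse event and the number with recurrent events, out of all enrolled children, each with an exact 95% CI.

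The cost is three rewordings and one extra pause code. Section 2.5.3 already has the timing and rationale of every pause recorded, and the per-child summaries in section 2.11.1 supply the data for (viii). The downside is a slightly stricter and more explicit set of targets. Nothing in treatment, safety monitoring or discontinuation changes.
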